### Assessments

Data collection will be based on an assessment protocol for gathering data on sociodemographic, physical, clinical, and biological variables. Patients from the two groups will be evaluated by blind raters at baseline (pre-intervention), after a 4-month intervention period, and 6-month follow-up period. Blood sampling for the analysis of biological parameters will be performed during the same visits. The control group will be evaluated only at baseline.

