### Statistical Analysis

A general descriptive analysis of the sample will be performed to assess baseline homogeneity. The normality of quantitative variables will be assessed by the Kolmogorov-Smirnov test and results will be expressed as means and standard deviation or as median values and interquartile range in the case of non-normal distribution. Qualitative variables will be expressed as frequencies and percentages.

To respond to the main aim, analysis of covariance (ANCOVA) will be used to assess the improvement in functionality. The same test will be used to analyze the difference between the groups.

At baseline, an analysis of variance (ANOVA) will be performed to confirm that there is no difference between patient groups, but there is a difference with the control group.

Student's *t*-test for related samples will be used to assess changes after the physical exercise program between intervention patient groups, among normally distributed variables. Changes in the variables studied across the three visits will be assessed by an analysis of repeated measurements. The analysis of repeated measurements will be used to assess the evolution of the variables studied during the three visits. Non-normally distributed variables will be assessed using Wilcoxon test. Univariate and multivariate regression analysis will be performed to determine whether statistically significant differences are associated with the evolution of the functionality and clinical and cognitive symptoms. All statistical analyses were carried out using SPSS v23.0 and R v3.5.0 statistical software, with the significance level set at *p* < 0.05.

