#### Sample Size

To calculate the sample size, a review of the literature related to the main topic of the study was carried out and using the Ene 2.0. computer program, it was determined that to obtain a power of 90% and an effect size of 0.65 with a significance of 5% and with possible losses to follow-up of 10% of the patients, it is necessary to have a sample of at least 38 patients per group to detect differences between the means of the main variables (EEAG and FAST). Therefore, we have estimated a sample size of 40 per group.

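### Comparing arms in the three-visit repeated-measures analysis with baseline as an ordinary outcome level would lose power against baseline adjustment

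*Protocol article*

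**What the plan says.** The Assessments section fixes the visits: "Patients from the two groups will be evaluated by blind raters at baseline (pre-intervention), after a 4-month intervention period, and 6-month follow-up period". Baseline is therefore one of the three.

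The Statistical Analysis section puts all three visits into one analysis, and says so twice: "Changes in the variables studied across the three visits will be assessed by an analysis of repeated measurements", and then "The analysis of repeated measurements will be used to assess the evolution of the variables studied during the three visits". It does not name the term that compares the arms, or the role of baseline.

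The main aim is handled separately: "To respond to the main aim, analysis of covariance (ANCOVA) will be used to assess the improvement in functionality". The next sentence adds: "The same test will be used to analyze the difference between the groups". No covariate and no visit is given for either. The only error rate is general, "with the significance level set at *p* < 0.05". The Sample Size section plans 40 patients per group, "with possible losses to follow-up of 10% of the patients".

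**The concern.** Baseline is measured before the intervention, so randomised arms can differ there only by chance. A baseline value says nothing about the treatment effect, but it predicts the later values well. Used as a covariate, it removes noise. Entered as one more outcome level in a conventional repeated-measures analysis, it adds noise, and the arm-by-visit test also spends a second degree of freedom.

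The repeated-measures sentences are the only ones in the Statistical Analysis section that name the three visits, and so the only ones tied explicitly to follow-up. Yet the Anticipant Results section expects benefit at both the post-intervention and follow-up visits in biological markers, retinal structure, anthropometrics, lifestyle and quality of life. If the arms are compared through this analysis, those questions get a weaker test than the same data could give.

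**Working it through.** **Plan's own figure.** The plan gives no power for the repeated-measures analysis. Its sample-size figure (38 per group; effect 0.65, 90% power, 5%) is for a simple difference in means. Two-sided, 2 × (1.960 + 1.282)² / 0.65² gives 50 per group, or 56 with 10% loss, so 38 is not reproduced. That is a separate matter and is not used here.

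**Inputs from the document.** 40 per arm less 10% gives n = 36; two arms, three visits; alpha 0.05, taken as two-sided because no side is stated.

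**Assumptions, not in the document.** SD 1 at each visit; the same correlation ρ between any two visits, 0.5, 0.6 or 0.7; effect 0 at baseline and 0.5 SD at both later visits.

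**Formulas.** For a one-degree-of-freedom test of effect δ with variance v per patient, the noncentrality is δ / √(2v/36), on the t distribution (70 df, or 69 with a covariate).

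- **A. Arm-by-visit, 2 df.** λ = (36/2) × Σ(δⱼ − mean δ)² / (1 − ρ). For effects (0, 0.5, 0.5) the sum is 0.1667, so λ = 3/(1 − ρ) = 6.0, 7.5, 10.0, on F with 2 and 140 df.
- **B. Mean of later visits minus baseline, 1 df.** v = 1.5(1 − ρ); noncentrality 2.45, 2.74, 3.16.
- **C. Baseline-adjusted, one later visit.** v = 1 − ρ² = 0.75, 0.64, 0.51; noncentrality 2.45, 2.65, 2.97.
- **D. Baseline-adjusted average of both later visits.** v = (1 + ρ)/2 − ρ² = 0.50, 0.44, 0.36; noncentrality 3.00, 3.20, 3.54.
- **E. Arm main effect over all three visits.** δ = (0 + 0.5 + 0.5)/3 = 0.333, two thirds of 0.5; v = (1 + 2ρ)/3 = 0.667, 0.733, 0.800; noncentrality 1.73, 1.65, 1.58.

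| Power, sustained 0.5 SD | ρ = 0.5 | ρ = 0.6 | ρ = 0.7 |
|---|---|---|---|
| A. Arm-by-visit | 57% | 68% | 81% |
| B. Change contrast | 68% | 77% | 88% |
| C. Adjusted, one visit | 68% | 74% | 83% |
| D. Adjusted, average | 84% | 88% | 94% |
| E. Main effect (only if used) | 40% | 37% | 35% |

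Against A, C gains about 10, 7 and 3 points. The gap from D to B is the cost of not using baseline as a covariate. The gap from B to A is the cost of the second degree of freedom.

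**Effect halving by follow-up (0.5, then 0.25 SD).** For A the sum of squares is 0.125, so λ = 2.25/(1 − ρ) = 4.5, 5.6, 7.5, and power is 45/55/68%. D (average effect 0.375) gives 60/66/74%. C at month 4 is unchanged at 68/74/83%. C at follow-up alone (0.25) gives 23/26/31%.

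**The protocol's own 0.65, sustained, ρ = 0.3/0.5/0.7.** A gives 66/81/96%, B 76/88/98%, C 81/88/97% and D 95/97/99%. A is the weakest of these four throughout, and the gap narrows as ρ rises.

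**The case against.** A reader might infer that the plan dilutes the arm effect by a third, because the effect is averaged with a visit where it is zero. The document does not support that. Only test E is diluted, and the plan never says that an arm main effect over all visits will be used. Its wording about changes and evolution points rather to visit or arm-by-visit terms, which are not diluted.

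A reader might also infer that the primary comparison is weakened. It is not, because the main aim goes to ANCOVA. The sentence on the difference between groups could extend ANCOVA to other variables and to follow-up, and the repeated-measures sentences do not mention groups. So the loss is conditional on comparing arms within the three-visit analysis.

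Three more points stand:

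- Having baseline as a response is not in itself an error. A three-visit model that constrains the baseline means to be equal between arms loses essentially nothing.
- The large gain is for the average of the two later visits. Visit by visit it is modest.
- Loss of patients with a missed visit follows from classical repeated-measures ANOVA, which the plan does not name.

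Finally, model terms and covariance structure may sit in an analysis plan that is not shown, and their absence is not the point here. What remains is the stated choice to analyse all three visits, baseline included, as repeated measurements, and to tie follow-up explicitly to that analysis alone.

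**Conclusion.** The point holds conditionally, as an efficiency matter in a supporting analysis. If arms are compared in the three-visit analysis with baseline as an ordinary outcome level, the arm-by-visit test gives up about 3 to 10 points of power against a baseline-adjusted comparison at one later visit. Against the adjusted average of both it gives up about 13 to 27 points (94 − 81 at ρ = 0.7; 84 − 57 at ρ = 0.5). These figures rest on 36 per arm, equal correlation of 0.5 to 0.7 and a sustained 0.5 SD effect. Only the 36 follows from the document.

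The change does not rescue a fading effect: at 0.25 SD the adjusted follow-up comparison stays at about 23–31%. The change is worth making because it is cheap and settles how the arms are compared at follow-up, but nothing here calls the primary ANCOVA into question.

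**What to change.** For between-arm comparisons over time, state a linear mixed model with the month-4 and follow-up values as responses. Fixed effects are baseline value, baseline-by-visit, arm, visit and arm-by-visit, with an unstructured covariance. Include every patient with at least one post-baseline value, so that partial data are used under the planned 10% loss. A three-visit model that constrains baseline means to be equal between arms is an equivalent alternative.

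Report the arm difference with its 95% CI at each later visit and for their average. The average is needed because most of the gain lies there.

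The cost is analysis wording only. SPSS and R, both named in the plan, fit this model, and no new data or visits are required.

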#### Sample Size

To calculate the sample size, a review of the literature related to the main topic of the study was carried out and using the Ene 2.0. computer program, it was determined that to obtain a power of 90% and an effect size of 0.65 with a significance of 5% and with possible losses to follow-up of 10% of the patients, it is necessary to have a sample of at least 38 patients per group to detect differences between the means of the main variables (EEAG and FAST). Therefore, we have estimated a sample size of 40 per group.

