#### Randomization and Blinding

FINEXT-BD patients will be randomly assigned to the groups (1:1) using Random Allocation Software version 1.0.0 software. Study evaluators will be blinded to the treatment branch. Patients will continue their usual treatment and will be treated by their reference psychiatrist, who will be informed of patient's participation in the interventionist program and will make sure that the appropriate clinical treatment is administered.

The flow diagram of the study can be seen in Figure 1.

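### The sample-size inputs do not give 38 per group: 90% power at effect size 0.65 needs 57 per group with 10% losses, and the planned 40 give about 78%

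*Protocol article*

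**What the plan says.** The Sample Size section reports a calculation made with a sample-size program after a literature review. The targets are "to obtain a power of 90% and an effect size of 0.65 with a significance of 5" per cent, with an allowance of 10% for loss to follow-up. The result is "at least 38 patients per group to detect differences between the means of the main variables (EEAG and FAST", and then: "we have estimated a sample size of 40 per group". Under Randomization and Blinding, allocation is 1:1.

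The Sample Size section does not say whether the test is one- or two-sided. It gives no standard deviation and no correlation between baseline and follow-up scores. The Statistical Analysis section names ANCOVA for the main aim, but the sample-size statement is framed as a difference between two means.

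**The concern.** A standardised difference of 0.65 with 90% power and a 5% test usually needs about 50 patients per group before any allowance for losses. A figure of 38 that already includes losses is well short of that. This is the article's only justification of the sample size for the primary aim, functional status. Readers will use the stated power to judge how much a non-significant result says about the absence of an effect. If the true power is nearer 78% than 90%, the chance of missing an effect of the planned size is about double what the plan tells them.

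**Working it through.** **Inputs**

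- Significance 5%, power 90%, effect size 0.65, losses 10%: Sample Size section.
- Comparison: difference between two group means (Sample Size), allocated 1:1 (Randomization and Blinding).
- Assumptions, because the section is silent: 0.65 is a standardised mean difference *d*, and the test is two-sided. A one-sided test is tried as a variant.

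**Step 1. Try to reproduce 38.** By the normal approximation, evaluable patients per group are n = 2(z₁₋α/₂ + z₁₋β)² / d².

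- 90% power, two-sided: 2(1.960 + 1.282)² / 0.65² = 2 × 10.51 / 0.4225 = 49.7, so 50. The exact *t* calculation gives 50.7, so 51.
- Allowing for losses: 51 / 0.9 = 56.7, so **57 per group** (56 by the normal approximation).

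The plan says 38, so its figure is not reproduced.

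**Step 2. Which settings do give 38?**

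| Setting (d = 0.65, 5%) | Evaluable per group, exact *t* | With 10% losses |
|---|---|---|
| Two-sided, 90% | 50.7 → 51 | 57 |
| One-sided, 90% | 41.2 → 42 | 47 |
| Two-sided, 80% | 38.1 (38 by normal approximation) | 44 (43 by normal approximation) |
| One-sided, 80% | 30.0 → 30 | 34 |
| Paired, two-sided, 90% | 26.9 → 27 | 30 |

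The only match is two-sided 80% power with no allowance for losses. That suggests how the number arose but does not prove it.

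**Step 3. Power at the plan's own numbers.** After 10% losses, 38 become 38 × 0.9 = 34.2, so 34, and 40 become 36. Exact *t*, d = 0.65:

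| Evaluable per group | Two-sided power | One-sided power |
|---|---|---|
| 34 (38 less 10%) | 0.752 | 0.843 |
| 36 (40 less 10%) | 0.776 | 0.861 |
| 38 (no losses) | 0.799 | 0.877 |
| 40 (no losses) | 0.819 | 0.892 |

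No entry reaches 0.90. The two readings of 38 should be kept apart: 75% if it includes losses, as the section says, and 80% if all 38 are evaluable. On the second reading 38 / 0.9 = 42.2, so 43 would have to be randomised, which is more than the planned 40.

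**Step 4. What 36 evaluable per group can detect.** Solving the two-sided *t* test for 90% power gives d of about 0.77 (0.80 with 34).

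**Step 5. Allowing for ANCOVA.** With a baseline-to-outcome correlation r, the effective effect is d / √(1 − r²). With 36 per group, two-sided:

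- r = 0.4: power 0.843
- r = 0.5: power 0.881
- r = 0.55: power 0.903

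The correlation needed for 90% is √(1 − (0.65 / 0.7747)²) = 0.54 with 36 evaluable, and √(1 − (0.65 / 0.7979)²) = 0.58 with 34.

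**The case against.** The best counter-argument is that the main aim will be analysed by ANCOVA, so the power of an unadjusted *t* test is not the power of the trial. This stands in part. If baseline and follow-up functioning correlate at about 0.55 or more, 36 evaluable patients per group do reach 90%. At lower correlations the shortfall is smaller than the unadjusted figure suggests: type II error is about 16% at r = 0.4 and 12% at r = 0.5. The trial's actual power is therefore unknown, and the 22% applies only to the unadjusted two-sided comparison. This does not support the stated figure, however. The section gives no correlation and describes a comparison of means, and a correlation it never mentions cannot justify the number it prints.

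A second defence is that the test might be one-sided, since the section does not say. It fails: 42 evaluable, or 47 with losses, would be needed, and even 40 with no losses fall just short at 0.892.

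A third is that the article condenses a longer protocol. That would excuse an omission. Here a printed result disagrees with the inputs printed beside it, and further detail would not make 38 follow from them.

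It is also fair to say that nothing in the article states that a null result will be read as no effect. That risk lies in how readers use the power figure.

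**Conclusion.** The concern holds. The stated inputs require 57 patients per group, not 38. With the planned 40 and 10% losses, the comparison described has about 78% power at an effect size of 0.65, so the type II error is about 22%, more than twice the stated 10%.

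This rests on reading 0.65 as a standardised mean difference, on a two-sided 5% test, and on no gain from baseline adjustment. Relaxing the sidedness leaves power at 86% with 36 evaluable. Only an unstated correlation of about 0.55 or more restores 90%.

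These figures also treat each of the two named main variables at the full 5%. If the significance level were split equally between them, power at 36 per group would be about 68%; the section does not say that it is split. Because the error lies in the main sample-size justification, it must be corrected.

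**What to change.** Keep 40 per group and restate what that number delivers, for example: *With 40 patients per group and 10% losses (36 evaluable), a two-sided 5% t test has about 78% power for a standardised difference of 0.65, and 90% power for a difference of about 0.77.*

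Alternatively, and closer to the planned analysis, base the statement on ANCOVA. Give the assumed correlation between baseline and 4-month scores with its source, and report the resulting power: 0.84 at r = 0.4, 0.88 at 0.5, 0.90 at 0.55. Either way, state the sidedness and say that 0.65 is a standardised difference.

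The cost is one reworded paragraph and a less favourable power figure, unless a correlation of about 0.55 can be supported. No extra patients are needed, and conduct and analysis do not change. By contrast, keeping the 90% claim for the unadjusted test would mean 2 × 57 = 114 patients, 34 more than the planned 80.

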##### Psychosocial functioning

The functioning of patients will be measured using *the Functioning Assessment Short Test (FAST*) (38). This scale is a brief instrument designed to assess functional impairment in psychiatric disorders. The scale comprises 24 items that cover six specific areas of functioning: autonomy, occupational functioning, cognitive functioning, financial issues, interpersonal relationships, and leisure time. Each item is scored in a 0–3 points range (0: no difficulty; 1: mild difficulty; 2: moderate difficulty; 3: severe difficulty) with total score ranging from 0 to 72 points (39).

The patient functionality will be assessed through the *Global Assessment of* Functioning (GAF) (40). This scale rates the level of functioning and severity of symptoms on a 0–100 scale, with higher values corresponding to better overall functionality.

Strauss-Carpenter scale (41). This scale will be employed to assess the psychosocial functioning of patients and consists of four items rated from 0 to 4 on a Likert-type scale and yields a total score that is calculated by the addition of all item scores: the higher the score is, the better the prognosis (42).

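### The main aim rests on two unranked scales (EEAG and FAST) under one undivided 5%, with no rule for whether one or both must succeed

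*Protocol article*

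**What the plan says.** The primary aim, given at the end of the Introduction, is improvement in functional status compared with patients who do not receive the intervention. It names no scale and no visit.

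The Sample Size section is the only place that ties the aim to instruments. The calculation is "to detect differences between the means of the main variables (EEAG and FAST", two variables with no order between them, and it is made "to obtain a power of 90% and an effect size of 0.65 with a significance of 5" per cent. That is one error rate and one effect size for two scales.

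The Statistical Analysis section answers the main aim by ANCOVA of functionality, again without a scale or visit. It adds a repeated-measures analysis over the three visits and covers all analyses "with the significance level set at" p < 0.05.

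The Assessments section places the post-baseline evaluations "after a 4-month intervention period, and 6-month follow-up period". Anticipant Results expects the functional gain over the TAU group when the exercise programme ends, but as an expectation and not as an endpoint definition.

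Psychosocial functioning describes FAST as a measure of functional impairment. Of the GAF it says: "This scale rates the level of functioning and severity of symptoms". The abbreviation EEAG occurs only in the Sample Size section and is not defined.

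**The concern.** With two main variables and one undivided 5%, the success rule decides what that 5% means, and the article gives none. A significant result on either scale could be presented as meeting the main aim, and the scale could be chosen once the results are known. The 5% would then apply to each test but not to the conclusion.

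If both scales had to succeed, the error rate would be safe, but the stated 90% power would not be the power of that joint event.

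This goes beyond a detail deferred to an analysis plan. The article does not leave the main variable open; it names two and gives them one 5%.

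**Working it through.** **Inputs.** From Sample Size: two main variables, 5% significance, 90% power, standardised effect 0.65, 10% losses, at least 38 per group and 40 planned. From Randomization and Blinding: 1:1 allocation. From Statistical Analysis: p < 0.05 throughout. Assumed, because the article does not give them: two-sided tests, and a correlation r between the two test statistics from 0 to 0.9, both scales oriented so that a positive value is benefit.

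**The plan's own figure.** For a comparison of two means, n per group = 2 × ((1.960 + 1.282)/0.65)² = 49.7, so 50. With 10% losses, 50/0.9 = 55.6, so 56. The stated 38 is not reproduced. It does match 80% power with no losses added: 2 × ((1.960 + 0.842)/0.65)² = 37.2, so 38. It would also be close under ANCOVA with a baseline correlation of about 0.55 to 0.6 (39 to 36 with losses), but none is stated. This is a separate matter. It is shown here because it affects how joint power should be read.

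**If either scale suffices.** With independent statistics, P(at least one p < 0.05) = 1 − 0.95² = 9.75%. With correlation r it is 1 − P(|Z1| < 1.96 and |Z2| < 1.96) for a bivariate normal. Counting only results in favour of exercise, it is 1 − P(Z1 < 1.96 and Z2 < 1.96).

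| r | At least one false positive, two-sided | At least one false claim of benefit |
|---|---|---|
| 0 | 9.75% | 4.9% |
| 0.3 | 9.5% | 4.8% |
| 0.5 | 9.1% | 4.5% |
| 0.7 | 8.3% | 4.2% |
| 0.8 | 7.8% | 3.9% |
| 0.9 | 7.0% | 3.5% |

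The single-test references are 5% and 2.5%. Every row exceeds them.

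**If both scales must succeed.** The chance that both are falsely significant is 0.25% at r = 0 and 3.0% at r = 0.9 when neither scale has an effect. It cannot exceed 5% when only one has an effect. The error rate is therefore controlled.

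For power, 40 per group less 10% leaves 36 completers. The expected statistic is 0.65/√(2/36) = 2.758, so unadjusted power on one scale is Φ(2.758 − 1.960) = 79%. Joint power on both scales is 62% at r = 0, 67% at r = 0.5 and 71% at r = 0.8.

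With baseline adjustment at an assumed baseline correlation of 0.5 to 0.6, the statistic is divided by √(1 − 0.5²) to √(1 − 0.6²). Single-scale power becomes 89% to 93%, and joint power 82% to 90% for r from 0.5 to 0.8.

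**The case against.** Several points on the other side have force.

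- **The inflation is conditional.** A reader might infer that the main claim simply fails to hold 5%. The article does not support that: it fails only under an either-scale rule, which is not written down. Under a both-scales rule the rate stays at or below 5%. The fault is the missing rule. This stands.
- **Four tests are not stated.** A reader might count two scales by two post-baseline visits, giving 1 − 0.95⁴ = 18.5% if independent and 9.4% at a common correlation of 0.9. The Statistical Analysis section never says that the ANCOVA is run at each visit. Its repeated-measures analysis could yield one test per scale, and Anticipant Results points to the end of the programme. Separate testing by visit would raise the rate, but the text neither states it nor rules it out.
- **The joint-power shortfall is mostly not due to having two scales.** A reader might set 62% to 71% against the stated 90% and blame the second scale. Unadjusted single-scale power is already about 79% with 36 completers, and the planned ANCOVA could recover much of the gap. What stands is only that the calculation was not made for joint success.
- **EEAG may not be the GAF.** The equation is plausible but unconfirmed. Any argument for FAST that rests on the GAF also rating symptoms depends on it. The count of two scales does not.
- **An unseen plan may set an order.** It may, so the absence of an order alone would be weak ground. The unranked pair under one 5% is in the text shown.

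**Conclusion.** The point holds in this limited form. The article fixes two main variables at one undivided 5% and gives no order, split or joint-success rule. If either scale can support the main claim, the two-sided error rate is about 7% to 9.75% over correlations from 0.9 to 0, and false claims of benefit about 3.5% to 5% against 2.5%. The assumptions are two-sided tests, jointly normal statistics, one test per scale and a correlation that the documents do not supply. No correlation in that range brings the rate down to 5%. If both scales must succeed, the error rate is sound and the gap is in the planning of power.

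**What to change.** State in the protocol, and repeat in the analysis plan:

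1. **Primary:** the between-arm difference in FAST total at the end of the 4-month programme, by ANCOVA adjusted for baseline FAST, two-sided 5%. FAST is described as a measure of functional impairment, which fits the aim, and the visit is the one Anticipant Results looks to.
2. **Next in order:** EEAG at 4 months at two-sided 5%, tested for a confirmatory claim only if FAST is significant.
3. **Follow-up results on both scales:** secondary.
4. **Terminology:** define EEAG and state whether it is the GAF of the Psychosocial functioning section.

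The cost is a few lines of text, no added patients and no power lost on FAST. The downside is that EEAG supports a confirmatory claim only after FAST succeeds. The change should be dated before anyone examines outcomes by arm, since only the evaluators are described as blinded.

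Other rules would also control the error rate. Requiring both scales needs a sample size planned for joint success. An equal split at 2.5% each needs 2 × ((2.241 + 1.282)/0.65)² = 58.8, so 59 per group, or 66 with 10% losses, for 90% power per scale without baseline adjustment. On the same basis one test at 5% needs 56; 40 are planned.
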